### Selection criteria for study subjects

At least one of the parents of the newborns meeting the inclusion criteria will be approached by the study investigator/nurse and informed of the study. A signed parental informed consent must be obtained.

### Exclusion criteria

1. Newborns with gestational age less than 36 weeks, with birth weights less than 1800 g, or admitted at the NICU after 6 hours of life.

2. Newborns with major congenital abnormalities or other syndromes that include brain malformations, congenital viral infections or evidence encephalopathy other than HIE.

3. Informed Consent refused.

### Allocation of participants to the trial groups (Randomization)

EEG is useful in identifying suitable newborns for hypothermia due to its capability to distinguish newborns with Sarnat grade 2 from those with Sarnat 1. Several studies have demonstrated that aEEG is easier to be interpreted than standard EEG, but equally accurate and reproducible. It correlates well with neurodevelopmental outcome of full-term infants with HIE, and it is considered the best single predictor of neurologic outcome. In some studies aEEG was more specific and exhibited a higher positive predictive value when compared with the neurologic examination performed in the first hours after delivery
[128-131].

In all three recruiting hospitals, randomization will be done stratifying eligible newborns according to aEEG into moderate or severe HIE. Newborns will be assigned to the group of moderate or severe aEEG to ensure maximal clinical homogeneity between the groups.

Newborns will be randomized in blocks of eight for each group, alternating newborns between TPM added to standard hypothermic treatment and standard treatment alone.

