#### Monitoring

The following respiratory and hemodynamic parameters will be registered before starting hypothermia and then at hours 0, 6, 12, 18, 24, 30, 36, 42, 48, 54, 60, 66, 72 of hypothermia, and after the re-warming process: respiratory rate, oxygen saturation (SaO_2_), fractional inspired oxygen (FiO_2_), systolic, diastolic and mean arterial pressures, heart rate. The following blood tests will be performed in all newborns at hypothermia hours 0, 24, 48, 72 and after re-warming process: blood gas analysis (corrected for body temperature), serum electrolytes, liver and renal function tests, creatine-kinase, creatine-kinase MB isoenzyme, lactate dehydrogenase, troponin IC, complete cell blood count, C-reactive protein, procalcitonin and coagulation tests.

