### Experimental plan and data analysis

Based on the medical literature, the mean incidence of the combined frequency of mortality and severe neurodevelopmental disability in survivors at 18 months of age is approximately 50%. In fact this percentage is 55% in the cool Cap study
[66], 44% in the NICHD study
[68], 45% in the TOBY trial
[69], 51.4% in the ICE trial
[70], and 50.9% in the neo.nEURO.network study
[71]. We hypothesize that treatment with TPM may reduce the incidence of the combined frequency of mortality and severe neurodevelopmental disability in survivors at 18 months at 15%. In order to compare the incidence of this primary outcome between newborns receiving TPM plus hypothermia (treated) and those only receiving hypothermia (control group), the estimated sample size was calculated, considering normal distribution, an alpha error of 0.05 and a power of 80 percent. The sample size for each group is 32 participants.

The three units have an overall admission rate of approximately 10 term newborns with HIE per year. Due to the high hypothetical advantages of this treatment, we estimate 90-100% rate of consent and we predict we would recruit the 64 newborns over around 24 months period with a realistic safety margin.

Mortality, the incidence of severe neuromotor disability, cortical vision, sensorineural hearing loss, developmental delay, epilepsy will be evaluated at 18 months of life.

To evaluate TPM safety, cardiac and respiratory parameters (heart frequency, blood pressure, oxygen saturation, respiratory support), will be continuously monitored. Blood samplings will be performed to check renal, liver and metabolic balance. Kruskal-Wallis test will be used to assess possible differences between newborns treated or not with TPM. The safety will be also evaluated by means of relative risk (RR)
[132]. RR will be calculated as the ratio between the probabilities of side effects in the TPM group with respect to the control group. Values of RR lower than 1, will be associated to the efficacy of the treatment.

Finally, we will evaluate the different distribution of any brain lesions on MRI brain highlighted.The RR is calculated for each item studied. An RR <1 indicates an improvement of neurological, neurodevelopmental and neuroradiologic hypothermia due to the association-topiramate.

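### Randomisation is stratified by aEEG class, but the comparisons the protocol names use neither the stratum nor the recorded baseline values, which gives away some precision

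*Protocol article*

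**What the plan says.** Under Allocation of participants to the trial groups (Randomization), the protocol article states that "In all three recruiting hospitals, randomization will be done stratifying eligible newborns according to aEEG into moderate or severe HIE", with blocks of eight within each class. Its reason is prognostic: of aEEG it says that "it is considered the best single predictor of neurologic outcome".

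Under Experimental plan and data analysis, the comparisons are:
- for safety measures, "Kruskal-Wallis test will be used to assess possible differences between newborns treated or not with TPM";
- for adverse effects, "RR will be calculated as the ratio between the probabilities of side effects in the TPM group with respect to the control group";
- for the neurological, developmental and MRI results, a relative risk item by item.

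No stratified or baseline-adjusted comparison is mentioned. No test or confidence interval is named for the primary outcome.

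Under Monitoring, respiratory and haemodynamic parameters "will be registered before starting hypothermia and then at hours 0, 6, 12, 18, 24" and so on to hour 72, and again after re-warming. Blood tests start at hour 0 of hypothermia. Usable baseline values are therefore part of the planned data.

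**The concern.** Stratifying balances the arms on aEEG class, so differences in risk between classes no longer add to the chance difference between arms. A crude comparison still counts that between-class variation as noise. Its standard error is then larger than the true sampling variability, its test rejects less often than its nominal level, and power is lost. The same applies to a continuous safety measure compared without its baseline value, except that there the loss comes from unexplained variation between infants.

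With 64 infants, precision is scarce. Safety is one of the two major objectives, and for a safety question a missed difference is the costly error.

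**Working it through.** **1. The plan's own figure.** The inputs, from Experimental plan and data analysis, are "an alpha error of 0.05 and a power of 80 percent"; a control risk given as "mean incidence of the combined frequency of mortality and severe neurodevelopmental disability in survivors at 18 months of age is approximately 50" per cent; and a risk under topiramate given as "combined frequency of mortality and severe neurodevelopmental disability in survivors at 18 months at 15" per cent, read as the rate reached. Two-sided testing is assumed, since sidedness is not stated. With p̄ = 0.325 and difference d = 0.35:

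n = [1.96√(2 × 0.325 × 0.675) + 0.8416√(0.5 × 0.5 + 0.15 × 0.85)]² / 0.35² = 26.9

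With continuity correction: (n/4)[1 + √(1 + 4/(nd))]² = 32.4. The stated 32 per group is reproduced (33 if rounded up). It is a crude two-proportion calculation.

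**2. Why the crude standard error is too large.** The risk in each stratum is not in the document and is assumed, with equal strata averaging 50%. The crude variance per infant under no effect is 0.5 × 0.5 = 0.25. The variance that matters after stratified allocation is the within-stratum mean:
- 30/70%: 0.3 × 0.7 = 0.21; √(0.25/0.21) = 1.09
- 20/80%: 0.2 × 0.8 = 0.16; √(0.25/0.16) = 1.25

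In large samples the crude SE is thus 9% to 25% too large under no effect.

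**3. Simulation at 32 per arm** (200,000 trials per scenario, arms balanced within stratum). The crude two-proportion z-test is set against the Cochran-Mantel-Haenszel (CMH) test. Power is at 50% v 15%, with a common RR of 0.3.

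| Control risk, moderate/severe | Type I, crude | Type I, CMH | Power, crude | Power, CMH |
|---|---|---|---|---|
| 50/50% | 6.0% | 6.0% | 87.6% | 87.3% |
| 35/65% | 4.8% | 5.1% | 88.1% | 88.8% |
| 30/70% | 4.0% | 4.9% | 88.7% | 90.2% |
| 20/80% | 1.9% | 5.0% | 90.3% | 93.8% |
| 37/100% (25 and 7 per arm) | 2.8% | 5.7% | 90.3% | 93.0% |

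The last row uses the Background figures by HIE grade: moderate 10% + 0.9 × 30% = 37%, severe 60% + 40% = 100%. The split of 25 and 7 brings the overall risk to about 50%. Those are clinical grades and any permanent disability, so they are only a rough proxy for aEEG class and severe disability.

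The mean crude SE of log RR under no effect, against its true SD, is 0.255 v 0.237 at 30/70% (8% too large) and 0.254 v 0.206 at 20/80% (23%).

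At smaller effects, crude v CMH power is:
- topiramate risk 25%: 56.6% v 59.3% (30/70%); 56.8% v 66.4% (20/80%)
- topiramate risk 30%: 38.5% v 41.0%; 37.3% v 47.2%
- topiramate risk 35%: 23.2% v 25.1%; 20.8% v 29.2%

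**4. Baseline adjustment of a continuous measure.** The variance factor is 1 − ρ², with the correlation ρ assumed: 0.91, 0.75 and 0.51 for ρ = 0.3, 0.5 and 0.7. For a 0.6 SD difference with 32 per arm, power rises from 67% to 71%, 79% and 92%.

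**The case against.** The strongest reply is that a protocol article commonly leaves covariates and stratified testing to the analysis plan, which is not shown. It adds that an item-by-item relative risk leaves room for a Mantel-Haenszel estimate. This stands in part: an unseen plan could add the stratum, and the explicit ratio definition is given only for side effects. But the article does name a two-group test and does define a ratio of group probabilities, so the point concerns stated methods and not only silence.

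The second reply is that the loss is modest and depends on assumptions. This stands. At 50% v 15% both analyses exceed the planned 80% power. At 20/80% the crude SE of log RR is then 0.492 against a true SD of 0.485. With a weak predictor nothing is gained: with 19 moderate and 13 severe infants per arm and control risks of 45/57.5%, power is 87.7% crude and 87.4% stratified.

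A reader might also infer more than the document supports:
- That error bars are misstated. None are stated; the excess width belongs to an interval that would accompany a crude RR.
- That the plan commits to over a hundred tests, by multiplying seven vital-sign measures by fifteen time points. The article does not say that Kruskal-Wallis is run at each time point.
- That unadjusted safety comparisons are confounded by baseline acidosis or instability. Randomisation balances baseline in expectation, so what is lost is precision, not validity.

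**Conclusion.** The point holds as one of efficiency. The named comparisons do not use the stratification factor or the baseline values. If aEEG is as prognostic as the protocol says, the crude analysis is conservative: at assumed control risks of 30/70% to 20/80%, type I error is about 2 to 4% instead of about 5%, and the null SE of log RR is about 8 to 23% too large. The power forgone is about 1.5 to 3.5 points at the planned effect and about 2 to 10 points at topiramate risks of 25 to 35%.

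These figures rest on assumed stratum risks and shares and on a common RR. They shrink to nothing as the predictor weakens. A reader might infer that the trial risks false positives or that 64 infants becomes too few. Neither follows: the error is in the conservative direction, and the sample size does not fail because of it. The correction is worth making because it is free, not because the stated analysis is invalid.

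**What to change.** State that the primary outcome and the other binary outcomes will be compared with a Mantel-Haenszel RR (or risk difference) with 95% CI and a CMH test, stratified by aEEG class as randomised.

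For continuous safety measures, replace the plain Kruskal-Wallis test with one of:
- a rank test stratified by aEEG class (van Elteren); or
- a simple baseline-adjusted model with arm, aEEG class and one baseline value.

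The baseline would be the pre-hypothermia reading for vital signs. For bloods it would be the hour-0 sample, provided it is drawn before the first dose. The article starts topiramate at the beginning of hypothermia and does not give the order, so this should be stated.

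A full arm-by-time repeated-measures model is not required and would be demanding with 64 infants. The cost is analysis wording only, plus a check of distributional assumptions if the model is chosen; no extra infants, visits or measurements are needed.

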**Methods/Design:**

Term newborns (gestational age ≥ 36 weeks and birth weight ≥ 1800 g) with precocious metabolic, clinical and electroencephalographic (EEG) signs of hypoxic-ischemic encephalopathy will be randomized, according to their EEG pattern, to receive topiramate added to standard treatment with moderate hypothermia or standard treatment alone. Topiramate will be administered at 10 mg/kg once a day for the first 3 days of life. Topiramate concentrations will be measured on serial dried blood spots. 64 participants will be recruited in the study. To evaluate the safety of topiramate administration, cardiac and respiratory parameters will be continuously monitored. Blood samplings will be performed to check renal, liver and metabolic balance. To evaluate the efficacy of topiramate, the neurologic outcome of enrolled newborns will be evaluated by serial neurologic and neuroradiologic examinations. Visual function will be evaluated by means of behavioural standardized tests.

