#### Hypothermia

All newborns who will satisfy admission criteria will be treated with moderate (33.5°C) hypothermia for 72 hours. Outborn patients will be initially cooled to 35°C at the birth hospital, avoiding heating and using ice packs during the transfer to NICU. In all the centers a cooling blanket with an esophageal probe will be used to induce hypothermia; the esophageal temperature will be lowered by the blanket’s servomechanism. Rectal temperature will be monitored by a rectal probe connected to cardiomonitor. After 72 hours of hypothermia, all newborns will be gradually re-warmed up to 36.5-37°C over the following 6–12 hours (0.5°C/h). Vital parameters will be continuously monitored under hypothermia.

Half of these newborns will be subjected to additional treatment with oral topiramate.

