#### Topiramate

TPM (Topamax, Janssen-Cilag, Cologno Monzese, Milan, Italy) will be administered by orogastric tube as enteric-coated granules mixed with water at the beginning of hypothermia for the first three days of life, for a total amount of 3 doses per patient. Newborns will receive 10 mg/kg once a day, a dosage usually used in infants
[111-113] and neonates
[114-117]. TPM plasma concentrations will be measured as previously reported
[118].

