### Neurological follow-up

The duration of follow-up necessary for possible neuro-motor disabilities and cognitive loss will be 24 months.

Every newborn will be evaluated beyond the neonatal period, at 1, 3, 6, 12, 18 and 24 months of life. Standard EEG will be evaluated within one week and will be repeated if abnormal. Within the first week and three months of age, newborns will be studied with Neonatal Hammersmith neurological examination and General Movement (GMs) assessment
[120]. The Hammersmith Infant Neurological Examination
[121,122] will be performed between 3 and 6 months of life. The mental and motor development will be evaluated with the Bayley Scales of Infant and Toddler Development 3^rd^ edition
[123] measure at 12, 18 and 24 months. Bayley scales will be used to measure the major areas of development: cognitive, language, motor, social-emotional and adaptive functioning.

Visual function will be assessed in the first ten days of life by means of a recently published battery of behavioural tests designed to assess various aspects of visual function
[124,125], which includes items that assess ocular movements (spontaneous behaviour and in response to a target), the ability to fix and follow a black/white target (horizontally, vertically, and in an arc), the reaction to a colored target, the ability to discriminate between black and white stripes of increasing spatial frequency, and the ability to keep attention on a target that is moved slowly away from the infant. Visual function will be evaluated again at 4 ½, 6 and 12 months with particular regards to binocular visual acuity, measured by means of standardized instruments based on preferential force choice (Teller acuity cards), stereopsis and ocular motricity.

Acoustic function will be monitored until 24 months.

Neurologists responsible of clinical follow-up will be blindfolded about which newborns have been treated with TPM in addition to hypothermia.

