#### Neuroradiologic follow-up

Standard cerebral magnetic resonance imaging (MRI), diffusion tensor imaging (DTI) and spectroscopy will be performed at the end of the hypothermic treatment within the first week, at three months and at 18 months.

Neuroradiologists responsible of follow-up will be blindfolded about which newborns have been treated with TPM in addition to hypothermia.

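### The allocation rule contradicts itself: infants are randomised in blocks of eight yet alternated between arms, which read literally makes the next assignment predictable

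*Protocol article*

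**What the plan says.** The section on allocation of participants first sets the strata: "In all three recruiting hospitals, randomization will be done stratifying eligible newborns according to aEEG into moderate or severe HIE". It then gives the rule for the sequence: "Newborns will be randomized in blocks of eight for each group, alternating newborns between TPM added to standard hypothermic treatment and standard treatment alone". Here each group means the moderate or the severe aEEG group. The Hypothermia section implies a 1:1 ratio: "Half of these newborns will be subjected to additional treatment with oral topiramate".

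Three other places bear on who can see the allocation:

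- **Comparator.** The abstract has infants randomised "to receive topiramate added to standard treatment with moderate hypothermia or standard treatment alone". No placebo is described there or in the Topiramate section, which says the drug "will be administered by orogastric tube as enteric-coated granules mixed with water".
- **Masking.** It is stated for two roles only. Under Neurological follow-up: "Neurologists responsible of clinical follow-up will be blindfolded about which newborns have been treated with TPM in addition to hypothermia". Under Neuroradiologic follow-up: "Neuroradiologists responsible of follow-up will be blindfolded about which newborns have been treated with TPM in addition to hypothermia".
- **Recruitment.** Under Selection criteria, at least one parent "will be approached by the study investigator/nurse and informed of the study". Under Ethical approval, consent precedes study entry.

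**The concern.** A randomised block has an unpredictable order. An alternating list has a fixed one, and cutting it into blocks of eight adds nothing. A site that follows the sentence as printed would run a quasi-randomised trial.

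Randomisation protects the comparison only if whoever decides on an infant's entry cannot foresee the arm. If the next arm can be foreseen, two routes to selection remain open: whether a particular family is approached, and whether a borderline tracing is classed as moderate or severe, since each class has its own next slot. The Inclusion criteria place the upper-margin boundary at above or below 10 μV, so a tracing at exactly 10 μV falls in neither class.

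The prognostic stakes are large. The Background gives mortality of 10% for moderate and 60% for severe encephalopathy. Masked outcome assessors guard against biased assessment. They do nothing about which infants entered which arm, and with 64 infants no later analysis reliably removes such a bias.

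**Working it through.** The article gives no figure for predictability, so there is none to reproduce. Its 32 per group serves only to give the total of 64. For 50% against 15%, alpha 0.05 and 80% power, a two-sided normal-approximation calculation with continuity correction gives 33 per group, close to the stated 32. Nothing below depends on that.

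**Inputs.** Total 64 infants (Experimental plan and data analysis). Block size 8, two aEEG strata and three hospitals (allocation section). The article does not say whether each hospital keeps its own lists, so the number of lists is either 3 × 2 = 6 or 2. Assumption throughout: the recruiter knows the earlier assignments on the list.

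**1. Continuous alternation, as the sentence literally reads.** Every assignment after the first on a list is certain.
- Six lists: (64 − 6)/64 = 58/64 = 91%.
- Two lists: (64 − 2)/64 = 62/64 = 97%.

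**2. Alternation restarting with a randomly chosen arm in each complete block of eight.** Seven of eight assignments are certain (87.5%), and the first is an even guess. Expected correct guesses: 7 + 0.5 = 7.5 of 8 = 94%.

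**3. True permuted blocks of fixed, known size eight at 1:1.** The recruiter always guesses the arm that is behind within the block. With block size 2m and m = 4, the expected number correct is

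m + (4^m / C(2m, m) − 1)/2 = 4 + (256/70 − 1)/2 = 4 + 1.33 = 5.33 of 8 = 67%.

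Enumerating all 70 possible blocks gives 66.6%. On average 1.6 of 8 assignments (20%) are known with certainty, because one arm is already full.

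**4. Random block sizes.** With assumed sizes 4, 6 and 8 and lists of 32 infants, a simulation in which the recruiter guesses from the running imbalance gives about 67.5% correct. That is no better than the fixed block of eight.

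**5. Reference.** A sequence that earlier assignments say nothing about gives 50%.

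**Can the recruiter know the earlier assignments?** The drug is given through an orogastric tube in the intensive care unit and the controls get no described counterpart, so bedside staff can be inferred to see the arm. With six hospital lists, the needed knowledge is local. With two shared lists, the 97% also requires knowing the last assignment at the other hospitals.

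**The case against.** The strongest reply is that *alternating* is loose English for 1:1 permuted blocks. Strict alternation needs no block, so the mention of blocks of eight points that way, and the full protocol may describe concealment. This is a real possibility, and it is why the point is framed as a contradiction. It does not rescue the text: the printed sentence is the only rule given, and on the kinder reading a fixed, known block with visible arms still leaves about 67% guessable. Nor does the point rest on concealment details being absent, which an article may leave to the full protocol. It rests on a stated rule.

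A second reply is that practice limits the opportunity. Admission after 6 hours of life is an exclusion, and even 64 infants in 24 months is only 32 a year across three units, so one infant can rarely be held back behind another. Expected consent of 90–100% leaves little room for steering through refusal. Both observations stand. Whom to approach and how to class a borderline tracing remain open.

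A reader might also infer several things the article does not support:

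- **That one team both recruits and grades the aEEG.** No section says who grades it.
- **That recruiters are told the block size.** This is not stated. Under alternation they would not need it; the 67% assumes it.
- **That severity varies widely within each aEEG stratum.** No figure is given. The allocation section says stratification is meant to make the groups homogeneous.
- **That the trial is declared open-label.** It is not. Visibility of the arm is inferred from the add-on design and from masking being stated for two roles only.
- **That steering three infants would mimic a drug effect.** Turning 16/32 against 16/32 into 13/32 against 19/32 with arm sizes held at 32 needs six infants exchanged, with their outcomes foreseen. The difference is 6/32 = 19 points. Its standard error is √(2 × 0.25/32) = 0.125, so z = 0.1875/0.125 = 1.5. The protocol's hypothesised effect is 35 points.

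**Conclusion.** Wrong as written. The rule combines two incompatible methods, and its literal reading is a predictable sequence. Under that reading, 91–97% of the 64 assignments are known in advance with continuous alternation, or 94% are guessed correctly if each block restarts at random. Under the kinder reading, with permuted blocks of a fixed, known size of eight, the figure is 67%.

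These figures rest on two assumptions: that staff see each infant's arm, and that the recruiter knows the earlier assignments on the list.

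The conclusion is that the rule permits selection bias, not that bias will occur. Its direction and size cannot be derived from the article.

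**What to change.** Delete *alternating* and replace the sentence with a rule along these lines:

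- Within each aEEG stratum, assignments follow a computer-generated random sequence in permuted blocks at 1:1, with the block size not disclosed to the sites.
- The arm is released only after eligibility, consent and aEEG stratum have been irrevocably recorded, either by central release or by sequentially numbered, opaque, sealed envelopes.
- State whether lists are held per hospital or shared.

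The random sequence and the concealed release are the working parts. Varying the block size alone adds little. Fixing the stratum before release closes the borderline-aEEG route.

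The cost is one reworded sentence, one generated list, and a set of envelopes or a simple central release step. It has to be done before enrolment, because selection at entry cannot be repaired afterwards.
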